# Effect of different ventilation modalities on the early prognosis of patients with sleep apnea after acute ischemic stroke–––protocol for a prospective, open-label and randomised controlled trial

**DOI:** 10.1186/s12883-023-03117-6

**Published:** 2023-06-06

**Keywords:** Sleep apnea, Acute ischemic stroke, High-flow nasal cannula, Nasal continuous positive airway pressure, Randomised controlled study

## Abstract

**Background:**

Sleep apnea is highly prevalent after acute ischemic stroke (AIS) and has increased stroke-related mortality and morbidity. The conventional sleep apnea treatment is continuous positive airway pressure (CPAP) ventilation. However, it is poorly tolerated by patients and is not used in all stroke patients. This protocol describes the impact of high-flow nasal cannula (HFNC) oxygen therapy compared to nasal continuous positive airway pressure (nCPAP) ventilation or usual care on the early prognosis of patients with sleep apnea after AIS.

**Methods:**

This randomised controlled study will be conducted in the intensive care unit of the Department of Neurology at the Wuhan Union Hospital. According to the study plan, 150 patients with sleep apnea after AIS will be recruited. All patients are randomly allocated in a 1:1:1 ratio to one of three groups: the nasal catheter group (standard oxygen group), the HFNC group, and the nCPAP group. Patients receive different types of ventilation after admission to the group, and their tolerance while using the different ventilation is recorded. Patients will be followed up by telephone three months after discharge, and stroke recovery is recorded. The primary outcomes were 28-day mortality, the incidence of pulmonary infection and endotracheal intubation.

**Discussion:**

This study analyses different ventilation modalities for early interventions in patients with sleep apnea after AIS. We will investigate whether nCPAP and HFNC reduce early mortality and endotracheal intubation rates and improve distant neurological recovery in patients.

**Trial registration:**

This trial was registered at ClinicalTrials.gov (NCT05323266; 25 March 2022).

## Background

Sleep apnea is one of the most common chronic diseases, affecting approximately one billion people worldwide [1]. However, its social and economic consequences mean that sleep apnea is a significant public health problem [2]. Sleep apnea, particularly obstructive sleep apnea (OSA), is more common in patients with acute ischemic stroke (AIS) and transient ischemic attack (TIA) (60–80%) [3, 4] and is associated with an increased risk of poor recovery, stroke recurrence and death [5, 6]. Currently, the oxygen therapy for patients with sleep apnea after AIS is continuous positive airway pressure (CPAP) [7, 8].

Early use of CPAP in patients with first ischemic stroke combined with sleep apnea (apnea–hypopnea index (AHI) ≥ 20 events/h) has been shown to improve neurological function significantly. In addition, CPAP prolongs the mean time from stroke onset to the first cardiovascular event [9]. However, CPAP could be unsuitable for patients with sleep apnea, as the mask and the elevated airway pressure during CPAP may induce sleep disturbances [10]. High-flow nasal cannula (HFNC) therapy is a new non-invasive respiratory support option that reduces upper airway collapse and lowers carbon dioxide levels at low positive pressure levels [11]. HFNC effectively reduces the AHI in children with sleep apnea, consistent with CPAP in children aged 7–14 [12, 13].

Therefore, we propose to conduct this clinical study in the intensive care unit of the Department of Neurology, Wuhan Union Hospital. The early prognostic value of different ventilation modalities on patients with sleep apnea after AIS will be clarified, laying the foundation for guiding clinical practice later.

## Methods and design

### Study design and setting

This prospective, open-label and randomised controlled trial will be conducted in the intensive care unit of the Department of Neurology at Wuhan Union Hospital. Enrolment of all participants begins on May 1, 2022. All participants with sleep apnea included are randomised according to 1:1:1 into the standard oxygen therapy group, the HFNC group and the nasal continuous positive airway pressure (nCPAP) group. Figure 1 demonstrates the flow chart of the study.

**Fig. 1 Fig1:**
[figure not shown]
Flow chart of the clinical trial

### Recruitment

In the clinical trial, we recruit participants with sleep apnea after AIS in the intensive care unit of the Department of Neurology, Wuhan Union Hospital. Recruitment is planned from May 1, 2022, to April 31, 2023. The recruited participants will be randomly grouped according to 1:1:1 into the standard oxygen therapy group, the HFNC group, and the nCPAP group. All participants will be informed in detail about the clinical trial and will provide written informed consent before recruitment. All patients will be followed up for three months after discharge, and the end date of post-discharge follow-up will be 31 July 2023. A detailed description of the trial's registration, interventions and assessment schedule is given in Table 1.

**Table 1 Tab1:** Timeline of the study

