**ASSESSMENTS:**							
**Baseline questionnaire**	X						
**Follow-up questionnaire**			X	X	X	X	
**Analyse data**							X

*t*_*1*_: treatment in hospital

*t*_*2*_: 1 week after discharge

*t*_*3*_: 1 month after discharge

*t*_*4*_: 3 months after discharge

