#### Secondary outcomes

1. National Institute of Health stroke scale (NIHSS). The NIHSS is used to evaluate the severity of stroke patients. Changes in NIHSS scores after one week in acute ischemic stroke patients with different ventilation modes. NIHSS scores range from 0–42, with higher scores indicating more severe neurological damage. 2. Barthel index. The Barthel index is used to assess the ability of stroke patients to live independently. This study assesses whether the quality of life of patients with acute ischemic stroke improves at one month and three months. 3. Sleep apnea symptoms. To assess changes in sleep apnea symptoms in patients with acute ischemic stroke. After one week of treatment with different ventilation modalities, polysomnography will be performed again to assess whether sleep has improved in stroke patients by calculating the magnitude of the AHI value. The minimum value of the AHI is 0, and there is no maximum value. A higher AHI value indicates more severe sleep apnea symptoms; 4. Time of hospitalization; 5. Cost of hospitalization; 6. Neurological recovery (mRS).

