### Data collection and follow-up

All participants in the clinical trial are assessed at baseline, and a specialist team member records information. Trial data includes baseline information (age, sex, height, weight, heart rate, blood pressure), previous medical history (history of surgery, family history, history of smoking and alcohol consumption), laboratory findings, imaging findings (brain MRI or CT), polysomnography findings, NIHSS score, mRS, Barthel Index, acute physiology and chronic health evaluation (APACHE) II score, GCS score, etc. Telephone follow-up is conducted one week, one month and three months after the participants are discharged from the hospital according to the plan developed for the study to assess the participants' neurological recovery and prognosis.

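### The 31 July 2023 end of follow-up does not fit recruitment to end April plus three months after discharge, and the discharge clock may put follow-up Barthel and mRS at different times since randomisation

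*Protocol article*

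**What the plan says.** All places are in the protocol article.

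- **Recruitment window** (Recruitment): "Recruitment is planned from May 1, 2022, to April 31, 2023".
- **Length and end of follow-up** (Recruitment): "All patients will be followed up for three months after discharge, and the end date of post-discharge follow-up will be 31 July 2023".
- **Clock for the calls** (Data collection and follow-up): "Telephone follow-up is conducted one week, one month and three months after the participants are discharged from the hospital". The notes to Table 1 agree, giving the last time point, t4, as "3 months after discharge". Table 1 places close-out and data analysis in August 2023.
- **Outcomes that depend on the calls** (Secondary outcomes): for the Barthel index, "This study assesses whether the quality of life of patients with acute ischemic stroke improves at one month and three months", with no time origin in that definition. The mRS is listed with no time point. That both are counted from discharge follows from Table 1 and the data collection section, not from the outcome definitions.
- **Length of stay** (Secondary outcomes): "Time of hospitalization" is itself compared between arms. No expected value is given.
- **Sign of a stay of about a week or more** (Secondary outcomes): "After one week of treatment with different ventilation modalities, polysomnography will be performed again".
- **Outcomes not counted from discharge**: 28-day mortality, and intubation and pulmonary infection after one week of ventilation (Primary outcomes); NIHSS change and repeat AHI at one week (Secondary outcomes).

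**The concern.** Two statements in the Recruitment section cannot both hold for the last recruits. A patient enrolled in the final days of April 2023 and kept in hospital for any ordinary length of time reaches three months after discharge in August, beyond the stated end. Whoever runs the follow-up must either break the promise of three months for every patient or overrun the date. If the date wins, the schedule itself creates missing three-month data, all of it in the latest recruits.

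The second issue is the choice of clock. Discharge happens after randomisation, in an open-label trial whose treatment is given in hospital, and the trial compares length of stay between arms. Recovery after stroke depends on time since the event. If one arm stays longer, its Barthel and mRS are taken later, and part of any difference could be due to timing.

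The measures are secondary but not marginal. The Sample size section builds the trial on rates of neurological recovery, and the abstract names later neurological recovery as something the trial will investigate.

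**Working it through.** **Inputs from the article:** recruitment from 1 May 2022 to the end of April 2023 (read as 30 April, 365 days); follow-up of three months from discharge; end date 31 July 2023; 150 patients; 10% loss allowance.

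**Assumed:** length of stay L of 7 to 28 days, because the article gives none; uniform recruitment; enrolment and randomisation on the same day.

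**Step 1. Can the stated date be reproduced?** 30 April 2023 + 3 months = 30 July 2023. So 31 July works if the three months run from enrolment, that is, with a stay of zero. If the impossible date is read as 1 May, the result is 1 August, which misses even with zero stay. Counted from discharge, 31 July is not reproduced.

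**Step 2. Latest discharge that fits.** 31 July − 3 months = 30 April 2023. With three months taken as 90 days it is 2 May 2023.

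**Step 3. End date needed and patients cut off.**

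- Last call needed = 30 April + L + 3 months.
- Latest recruitment date that still meets 31 July = 30 April − L.
- Recruitment rate = 150 / 365 = 0.411 per day.
- Patients cut off = 0.411 × L.
- Days from enrolment to the three-month call = L + 91.

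| Assumed stay L (days) | Last call needed | Latest recruitment date that fits | Patients cut off (% of 150) | Same, three months = 90 days | Days from enrolment to call |
|---|---|---|---|---|---|
| 7 | 7 August | 23 April | 2.9 (1.9%) | 2.1 | 98 |
| 14 | 14 August | 16 April | 5.8 (3.8%) | 4.9 | 105 |
| 21 | 21 August | 9 April | 8.6 (5.8%) | 7.8 | 112 |
| 28 | 28 August | 2 April | 11.5 (7.7%) | 10.7 | 119 |

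**Step 4. Against the loss allowance.** 10% of 150 is 15 patients. Stays of 7, 14 and 21 days use about 3, 6 and 9 of those 15. The Missing data plan moves from complete cases to multiple imputation at 10% missing. With 6 patients lost to the calendar, 15 − 6 = 9 other losses would reach that threshold.

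**Step 5. Effect of the clock.** Any difference in mean stay passes one for one into time at assessment. Mean stays of 7 and 14 days in two arms would give calls at 98 and 105 days, 7 days apart. The article gives no figure from which an effect on Barthel or mRS could be derived.

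**Step 6. Counting from randomisation.** 30 April 2023 + 90 days = 29 July 2023, inside the stated end date.

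**The case against.** The strongest reply is that this is a slip in a date. The sentence that sets the end date also promises three months to every patient, and a trial team would probably honour the promise. Table 1 puts close-out in August 2023, and for the stays assumed above the last calls would still fall within that month. Even if the date were enforced, the loss alone stays below 10%. This limits the size of the problem but does not remove the contradiction. August is assigned to analysis, and the 10% was set for deterioration and for loss after discharge, so a calendar loss comes on top.

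A reader might infer three stronger things that the article does not support.

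- **That outcomes are taken at arm-dependent times.** Listing length of stay as an outcome shows that it will be compared, not that it differs. The discharge clock creates a risk that becomes real only if stay differs by arm.
- **That the primary outcomes are damaged.** None of them is counted from discharge, nor are the one-week NIHSS and AHI.
- **That 28-day mortality cannot be established because no call falls on day 28.** No call on that day is needed. For anyone discharged alive, the call one month after discharge falls after day 28 from enrolment, and hospital records cover those still admitted. How deaths enter the Barthel and mRS analyses is commonly left to the analysis plan, which is not at hand.

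It can also be said that a new clock comes late. The article appeared on 6 June 2023, after planned recruitment had closed, so many discharge-timed calls would already have been made. That stands, and the fix allows for it.

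**Conclusion.** The Recruitment section contradicts itself, and this rests on calendar arithmetic alone: 31 July 2023 suits only patients discharged by about 30 April 2023 (2 May if three months means 90 days). How many patients are affected depends on the assumed stay and on even recruitment, and matters only if the date is enforced. It is a small share of 150, confined to the three-month Barthel and mRS.

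The remark on the clock is conditional. Discharge is a weak time origin for comparing arms because treatment may affect it, but the article gives no evidence that stay will differ. The point is worth correcting because the remedy is cheap and protects the three-month functional comparison. It is not a threat to the primary results.

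**What to change.** 1. Correct the recruitment end date, since April has 30 days.
2. Move the end of follow-up to the last discharge plus three months, in August 2023 or later, and start the analysis after that. This alone cures the contradiction. It costs an amendment and a delay of roughly the last patient's hospital stay.
3. Preferably, time the one-month and three-month Barthel and mRS from randomisation, and state that origin in the outcome definitions. All arms then share one clock and the stated end date holds. The cost is a revised call schedule. The small downside is that some patients will be assessed while still in hospital.
4. Where calls have already been made on the discharge clock, record days since randomisation at each Barthel and mRS assessment and report the distribution by arm. Adjust for it, or show its influence in a sensitivity analysis. Because time at assessment is itself determined after randomisation, the adjusted result is better read as a check than as a replacement for the main comparison. This costs only one derived variable.

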	**STUDY PERIOD**						
	**Enrolment**	**Allocation**	**Post-allocation**				**Close-out**
**TIMEPOINT**	***May 2022—April 2023***	**May 2022—April 2023**	***t***_***1***_	***t***_***2***_	***t***_***3***_	***t***_***4***_	***August 2023***
**ENROLMENT:**							
**Recruitment**	X						
**Eligibility screen**	X						
**Informed consent**	X						
**Allocation**		X					
**INTERVENTIONS:**							
**standard oxygen group**			X	X	X	X	
**HFNC group**			X	X	X	X	
**nCPAP group**			X	X	X	X	
**ASSESSMENTS:**							
**Baseline questionnaire**	X						
**Follow-up questionnaire**			X	X	X	X	
**Analyse data**							X

*t*_*1*_: treatment in hospital

*t*_*2*_: 1 week after discharge

*t*_*3*_: 1 month after discharge

*t*_*4*_: 3 months after discharge

### Inclusion criteria

1. Age ≥ 18 years; 2. Clinical diagnosis of AIS; 3. Diagnosis of AIS confirmed by CT and MRI; 4. National Institutes of Health Stroke Score (NIHSS) baseline score of 2–20; 5. State of consciousness (Glasgow Coma Score (GCS) of ≥ 9); 6. Semi-quantitative cough strength score of ≥ 2.

### Exclusion criteria

1. Pre-existing obstructive sleep apnea; 2. Suspected sleep disorders other than sleep apnea (e.g., episodic sleeping sickness); 3. Respiratory distress requiring mechanical ventilation; 4. Oxygen-dependent chronic obstructive pulmonary disease; 5. Pregnancy; 6. Intracranial haemorrhage; 7. Inability to use a nasal mask or mask (e.g., facial trauma); 8. Patients who died within 24 h of admission; 9. History of other neurological disorders such as Parkinson's, neuro infection, and neuromuscular disease patients; 10. Hospice care or comfort measures only; 11. Inability to provide informed consent; 12. Inability to provide valid information; 13. Suicidal ideation.

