### Withdraw criteria

1. Unable to tolerate the clinical trial and requesting an early withdrawal. 2. Patient is unsuitable for further trials due to deterioration. 3. Poor compliance with the follow-up plan.

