### Sample size

The sample size is calculated using the Contingency Table (Chi-Square Tests) in the PASS 15.0 software. A literature review showed that nCPAP was approximately 65% effective for neurological recovery in stroke patients and 55% effective for HFNC, compared to 40% in the standard oxygen therapy group [14, 15]. In this study, the test level α = 0.05 and the test efficacy 1-β = 0.9. The final sample size is expected to be 150 cases, considering a 10% loss to follow-up rate, including the possibility of deterioration after admission and loss to follow-up after discharge.

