### Randomisation and blinding

All participants are informed of the trial's purpose and sign an informed consent form. Participants will be randomised by block randomisation in the randomisation tool (www.randomisation.com). The randomisation sequence is assigned by an independent statistician using a random block size of 6 and 9 in a 1:1:1 fashion. The randomised numbers are placed in opaque sealed envelopes, and participants entering the group will be randomly given one of the envelopes and a grouping result based on the number. The data analysts in this study will not be involved in any interventions and will remain blinded to group allocation. The trial is open, as the researcher and participants cannot mask group allocation.

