### Study outcomes

#### Primary outcomes

1. 28-day mortality rate; 2. Tracheal intubation rate (Rate of tracheal intubation in each group after one week using different ventilation methods); 3. Pulmonary infection rate (Rate of pulmonary infections in each group after one week using different ventilation methods).

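### Exclusion 8 (death within 24 h of admission) cannot be assessed at enrolment and, as written, allows a randomised patient's death to be taken out of 28-day mortality

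*Protocol article*

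**What the plan says.** In the protocol article, item 8 of the Exclusion criteria is "Patients who died within 24" hours of admission. The first item under Primary outcomes is the "28-day mortality rate".

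On the order of events, the Recruitment section says that participants "will provide written informed consent before recruitment". Randomisation and blinding says that "participants entering the group will be randomly given one of the envelopes". The Methods paragraph of the abstract adds: "Patients receive different types of ventilation after admission to the group". None of these gives a number of hours from admission to randomisation, or a minimum survival time before it.

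On masking, Randomisation and blinding states: "The trial is open, as the researcher and participants cannot mask group allocation". Only the data analysts are kept blind.

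**The concern.** An eligibility criterion should be answerable when the patient is screened. This one is answered by what happens afterwards. A patient who has already died cannot consent or be randomised, so the criterion adds something only for a patient who was enrolled less than 24 h after admission. For that patient it can be applied only in retrospect, once the death has occurred.

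Any death it removed after randomisation would be a primary-outcome event, removed because it was one. Such removal would lower the reported mortality of the arm concerned. If early deaths were not spread evenly over the three ventilation arms, it would also distort the comparison between them. Staff who know the allocation would be the ones to judge such a patient ineligible, and assigned ventilation might already have begun. What is at stake is whether 28-day mortality compares the groups as randomised.

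**Working it through.** The plan gives no figure to reproduce on this point. The check is a reading of the sections on timing, followed by an illustration under assumed rates.

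**Step 1: when can item 8 act?**

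- Death before randomisation: the patient never enters the trial, with or without item 8. No effect.
- Randomisation later than 24 h after admission: every randomised patient has already outlived the window. No effect.
- Randomisation within 24 h, then death before hour 24: item 8 is met by a randomised patient. This is the only case in which it matters.

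**Step 2: do the sections rule out the third case?**

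- Recruitment, Randomisation and blinding, and the abstract give the order (consent, envelope, ventilation) but no interval from admission.
- Table 1 puts the eligibility screen in the enrolment column, ahead of allocation. That is an order of steps, not a minimum time.
- Study design and setting has only patients with sleep apnea randomised, but the Inclusion criteria set no sleep-apnea criterion and no section dates the diagnostic sleep study. The full-night polysomnography described under Intervention groups is for titration, after allocation.
- Sample size allows for losses "including the possibility of deterioration after admission and loss to follow-up after discharge". This names reasons for loss and does not fix the time of randomisation either way.

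The third case is therefore not excluded.

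**Step 3: size, under assumed rates.**

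From the article: 150 patients allocated 1:1:1, so n = 150/3 = 50 per arm. Assumed, because the article gives neither: 28-day mortality m of 5% to 20%, and a share e of those deaths within 24 h of admission of 5% to 30%. A third unknown is r, the share of those early deaths that fall after randomisation.

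- Deaths per arm: D = n × m
- Deaths removed per arm: k = D × e × r
- Reported mortality: (D − k)/(n − k)

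With r = 1, the worst case:

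| m | e | D per arm | k per arm | Reported mortality | Removed in trial (3k) |
|---|---|---|---|---|---|
| 5% | 5% | 2.5 | 0.125 | 4.8% | 0.4 |
| 10% | 10% | 5 | 0.5 | 9.1% | 1.5 |
| 10% | 20% | 5 | 1 | 4/49 = 8.2% | 3 |
| 20% | 30% | 10 | 3 | 7/47 = 14.9% | 9 |

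The number removed scales directly with r. At r = 0.5 the range of 0.4 to 9 deaths becomes about 0.2 to 4.5, and at r = 0 nothing is removed.

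**Step 4: unequal removal, also assumed.** Take three arms with 5 deaths in 50 each (10.0%) and remove 0, 1 and 2 deaths. The arms then report 5/50 = 10.0%, 4/49 = 8.2% and 3/48 = 6.3%. This shows how sensitive so few events are. It does not forecast such an imbalance.

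**The case against.** A reader might infer that the trial will remove randomised patients' deaths and so report mortality that is too low, or hide early harm from one of the ventilation modes. The article does not support that reading, for four reasons.

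- No section says that anyone is removed after randomisation under item 8. Table 1 places eligibility screening before allocation, and removal after entry has its own list, Withdraw criteria. That list includes "Patient is unsuitable for further trials due to deterioration" but not death within 24 h. Read in its place, item 8 may simply mean that patients who die on the first day never enter.
- Early randomisation looks unlikely. Only patients with sleep apnea are randomised, and pre-existing obstructive sleep apnea is an exclusion, so at least the obstructive form has to be newly identified. Data collection and follow-up counts polysomnography among the trial data, and Secondary outcomes has it repeated after one week, which implies an earlier study. Imaging confirmation of the stroke and written consent also come first. Together these could take up much or all of the first 24 h.
- Deaths in the first hours should be uncommon in patients with NIHSS 2–20, GCS of at least 9 and adequate cough strength, who can consent and do not need mechanical ventilation at entry.
- Naming the analysis population is commonly left to the full protocol or the SAP, so its absence from an article is no finding.

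Most of this stands, and it makes the consequence conditional and its probable size small. It does not clear the criterion. One overnight sleep study can finish within 24 h of admission, and no section sets a minimum interval. The point also concerns a rule that the article does state, not an omission: an all-randomised analysis defined elsewhere would sit awkwardly with a rule that makes these patients ineligible.

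**Conclusion.** Item 8 is a drafting defect whatever the timing: it is either redundant or an exclusion after randomisation on a primary outcome. The article does not settle which. If every patient is randomised more than 24 h after admission, it does nothing. If some are randomised earlier, following it as written would remove any death between randomisation and hour 24 from 28-day mortality, in a trial where treating staff know the allocation.

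The size cannot be derived from the article. A drop from 10.0% to 8.2% in one arm illustrates the loss of a single death out of 5, and the table's upper figures treat every death within 24 h of admission as occurring after randomisation. For this population both the early share and r are probably low, so the likely effect is small and may be nil. The article does not support a claim that the mortality result will be biased.

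**What to change.** Either delete item 8 from the Exclusion criteria, or restate it as a condition checked only before randomisation, namely that the patient is alive 24 h after admission when randomised. In both cases add that no randomised patient is excluded because of death and that every death after randomisation counts in 28-day mortality.

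Deletion is simpler and leaves the timing of enrolment as it is. The restated version would hold randomisation back to 24 h after admission, which changes practice only if some patients are now randomised earlier. The cost is one line of text, with Ethics Committee approval where the section on modification of the protocol requires it. Observed mortality may read slightly higher than under the present wording.
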